## Materials and methods

Design and setting

This is a quasi-experimental study. There will be one intervention group and one control group. The groups can be considered parallel groups. The participant allocation ratio (intervention: control) will be 1:1. The study will be conducted in the selected sub-districts of Bangladesh - Bogura Sadar and Chapai-Nawabganj Sadar. Bogra Sadar is an upazila of Bogra District in the Division of Rajshahi, Bangladesh. Nawabganj Sadar is an upazila of Nawabganj District in the Division of Rajshahi, Bangladesh. There are 64 districts and eight divisions in Bangladesh [6]. The study sites have been selected purposefully, considering sociocultural factors such as the fact that both study sites are agriculture-based societies. Both are disaster-prone areas of Bangladesh and both are semi-urban in nature. These criteria are in line with the study's purpose.

Study population

Inclusion and Exclusion Criteria

Inclusion criteria: Women and adolescent girls with disabilities who fulfill the following inclusion criteria - the age range for adolescent girls with disabilities: 10 to <18 years; the age range for women with disabilities: 18 to 45 years; the women and adolescent girls with disabilities are menstruating women and adolescent girls; women and adolescent girls with physical or hearing or visual or combined disability; and duration of stay at the study site: more than or equal to six months. Inclusion criteria for the male counterparts - relationship status with the female participant, i.e., husband, father, or elder brother; age limit: 18-65 years; and duration of stay at the study site: more than or equal to six months.

Exclusion criteria: Women and adolescent girls who meet the following exclusion criteria as well as their male counterparts will be excluded from this study: persons who are presently pregnant, have any mental and intellectual disabilities, have a terminal illness, and all those unable to provide informed consent.

Sample Size

We calculated the sample size using the G Power software (version 3.1.9.4) [7]. The software has been developed by Axel Buchner, who is associated with Heinrich Heine University Düsseldorf, a public university in North Rhine-Westphalia, Germany, founded in 1965 [8]. Analysis of variance for repeated measures within-between interactions assumed a medium Cohen's effect size of 0.13 [9].

Bangladesh has a patriarchal society that is dominated by men [10]. The topic of menstruation is taboo in society [11]. During follow-up, there is a substantial risk of participant loss, particularly for the male counterparts. When taken into account in the socio-cultural context, those lost to follow-up are regarded as 30%. Considering the lost-to-follow-up rate, a total of 156 (78 - intervention and 78 - control) women and adolescent girls with disabilities were recruited in the study.

Recruitment Process

Two community health workers have been recruited for the study from the 'Organization of People with Disabilities'. The lead investigator provided them with training and supportive supervision. 'Organization of People with Disabilities' is a root-level organization that especially works for people with disabilities at the community level. The recruited community health workers will meet with community members door-to-door. They will use "Washington Group Short Set Questionnaires on Functioning” for disability screening. The questionnaire set has questions on visual, hearing, walking, concentration, communication ability, and self-care [12]. It is a disability identification tool using which it is possible to identify those who are at risk of disability. From the positively screened individuals with disabilities, study participants will be recruited. Male counterparts’ involvement will be considered a critical intervention in the study. In the intervention group, male counterparts (father, husband, and brother) of the women and adolescent girls with disabilities will also be included as study participants. The study will consider these male peers' involvement and participation in managing menstrual hygiene as the key interventions. The study will run from April 2022 to March 2025.

Interventions

Figure 1 shows the procedure of the study. The intervention group will receive 10 months of health education on menstrual hygiene management as well as the role of male counterparts in managing menstrual health and hygiene. Blinding will not be used in this study. Community health workers will visit the study participants on a door-to-door basis. They will provide health education information in one-on-one meetings and courtyard sessions.

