## Abstract

Background

Women and adolescent girls with disabilities suffer the most difficulties during menstruation days in developing countries like Bangladesh. They deal with menstruation in a hazardous and unclean manner. In Bangladesh, men serve as the family's gatekeepers for health-seeking behavior. But they frequently have no idea how unpleasant and demanding menstruation can be. Menstrual hygiene care for women and adolescent girls with disabilities can be improved by involving male peers. In Bangladesh, no such intervention has been assessed. The purpose of the study is to assess the effects of male participation on menstrual hygiene management of women and adolescent girls with disabilities in Bangladesh.

Methods

This will be a quasi-experimental study with a sample size of 120 (60 - control, 60 - intervention). The study will be conducted in a sub-district of Bogura and Chapainawabganj in Bangladesh. Inclusion criteria for the study participants are women and adolescent girls with disabilities (intervention and control groups) and male counterparts (intervention group). The exclusion criteria for this study are women and adolescent girls with mental and intellectual disabilities. Engaging male peers in menstrual hygiene management is the key intervention in the study. No blinding or randomization will be applied. The expected primary outcome in the intervention group will be an improvement in the menstrual hygiene management of women and adolescent girls with disabilities in the selected sub-districts of Bangladesh. Two times data will be collected from the intervention and control groups using the ‘Menstrual Practice Needs Scale-36’, ‘Perceived Stress Scale’, and ‘Multi-dimensional Scale of Perceived Social Support’. The analysis of variance (ANOVA) test will be applied to a two-point data series to assess statistical significance.

Results

The result of the study will be published in a scientific journal. The outcomes of the research will be disseminated to local policymakers and health planners. The health administrator will get evidence-based information on gender-inclusive menstrual hygiene management for women and adolescent girls with disabilities through study result dissemination events.

Conclusion

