The Multi-dimensional Scale of Perceived Social Support will be used to assess perceived social support among women and adolescents with disabilities. The multi-dimensional scale of perceived social support is divided into three sub-scales: family subscale, friends subscale, and significant other subscale. Any mean scale score between 1 and 2.9 could be regarded as low support while scores between 3 and 5 could be regarded as moderate support. and scores between 5.1 and 7 might be regarded as high support [18,19]. The Bangla version of the scale will be used.

Data collection and follow-up

We will collect data at baseline, after 10 months of health education intervention. The data collection tool will be the Kobo Toolbox, which is a real-time data collection tool [20]. The researchers are using the Kobo Toolbox as a data collection and monitoring instrument. Community health workers will go door-to-door. Participants will be interviewed one-on-one. The interview will be performed utilizing a Kobo Toolbox-embedded questionnaire.

Methods of Monitoring

Global positioning system mapping will be embedded in the questionnaire for monitoring purposes. In addition, community health workers will send activity photos and recorded interviews with the prior consent of the participants. Triangulation of the GPS map, photos, recorded audio files, and real-time communication with field staff will ensure quality data collection and following steps. Principal investigators will visit the fields periodically if needed.

Data Quality Control

Data cleansing will be done following data collection. It covers handling missing values, outliers, and inconsistencies. Accuracy, consistency, and dependability will be ensured by performing checks on data validation, reconciliation, and profiling. To increase confidence in the data and ensure trustworthy insights, a thorough data quality control method will be used.

Data Analysis Plan

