SPSS version 28.0 (IBM Corp., Armonk, NY, USA) will be used for data analysis. Descriptive statistics on participant particulars (age, household income, age of menarche, education level) will be explored. Menstrual practice needs, perceived stress, and perceived social support will be measured in the control group and the intervention group. An analysis of variance (ANOVA) test will be applied to test variations in responses among different disability groups. There will be two time-point measurements of menstrual practice needs, perceived stress, and perceived social support, using the study scales. An ANOVA test will be applied to the study data sets due to the two-point measurements of needs, stress, and support. During data analysis, potential confounders will be adjusted.

Reporting Guideline/Checklist

This protocol has been developed in accordance with the Guidelines for Reporting Outcomes in Trial Protocols: The SPIRIT-Outcomes2022 Extension [21]. The reporting of findings of the intervention will be informed by the Transparent Reporting of Evaluations with Nonrandomized Designs (TREND) guidelines [22]. Important amendments to this protocol will be published along with the results of the intervention.

Risks

This non-invasive study will proceed without dealing with bio-specimens. There is no scope for harm considering physical, mental, social, economic, racial, or political perspectives. All the collected data will be dealt with anonymously, and only the study team can access the data for research purposes only.

Ethical considerations

The study protocol has been approved by the Institutional Review Board of the National Institute of Preventive and Social Medicine (NIPSOM), Dhaka, Bangladesh. Memo No.: NIPSOM/IRB/2023/07. During recruitment, participants will provide their informed written consent. Before receiving informed written consent, participants will be briefed about the study objectives, study procedures, and measures to ensure privacy and anonymity. They will also be informed that they could withdraw from the study at any point in the project. The legal guardian will provide informed assent on behalf of the participant when her age is below 18.

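### The sample size and the planned ANOVA make no allowance for shared courtyard sessions or for the two sub-districts, so the error may be understated and, if each group is one sub-district, site cannot be separated from intervention

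*Protocol article*

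**What the plan says.** All references are to the protocol article.

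- **Sites** (Design and setting): "The study will be conducted in the selected sub-districts of Bangladesh - Bogura Sadar and Chapai-Nawabganj Sadar". They were not sampled: "The study sites have been selected purposefully". The reasons given are that both are agricultural, semi-urban and disaster-prone. There is one intervention group and one control group at 1:1, and the Abstract rules out randomisation. The text does not say whether each sub-district is one group or both groups are recruited in each. Figure 1 may show this but is not available here.
- **Delivery** (Recruitment Process, Interventions): two community health workers were recruited for the study. On the education they give: "They will provide health education information in one-on-one meetings and courtyard sessions". The Introduction directs the courtyard sessions at family members of the women in the intervention group. The control group receives the usual family planning services.
- **Sample size** (Abstract, Sample Size): "This will be a quasi-experimental study with a sample size of 120 (60 - control, 60 - intervention"). The basis is "Analysis of variance for repeated measures within-between interactions assumed a medium Cohen's effect size of 0.13". The rise to 156 is attributed only to 30% loss to follow-up (120 × 1.30 = 156). No design effect, ICC or session size is given.
- **Analysis** (Data Analysis Plan): "An ANOVA test will be applied to the study data sets", because there are two measurements. Potential confounders are to be adjusted for, without being named.

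**The concern.** Both the sample size and the named test treat every woman as a separate, independent observation. Two features of the design may break that.

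First, women who share a courtyard session, or whose families do, hear the same content in the same setting. Their changes over 10 months may be more alike than those of unrelated women. The ANOVA counts them as independent, so its standard error is too small by an amount that depends on the session size and the ICC.

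Second, if one sub-district is the intervention group and the other the control group, the group-by-time effect also contains anything that changed differently between the two places: a local disaster, another programme, a change in product supply. The p-value would then include no variation between sites.

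In either case, correlation within sessions or a local change could be reported as an effect of male involvement, in a study meant to inform policy.

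**Working it through.** **1. The plan's own figure.** Inputs from the article: f = 0.13, two groups, two time points, within-between interaction. Not stated and therefore assumed: alpha 0.05, power 0.80, pre-post correlation ρ = 0.5.

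Noncentrality λ = f² × N × m / (1 − ρ), with m = 2 time points, df 1 and N − 2.

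At N = 120: λ = 0.0169 × 120 × 2 / 0.5 = 8.112 and power is 0.807. The smallest even N reaching 0.80 is 120, so the stated figure is reproduced. Changing one assumption loses it: ρ = 0.3 gives 166, ρ = 0.7 gives 72, and power 0.90 at ρ = 0.5 gives 158. On this reconstruction, 120 is a calculation for independent women with nothing left for clustering.

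**2. Shared sessions in the intervention group only.** Session size c and ICC are not in the article; the ranges are assumptions.

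- Design effect in the intervention group: DE = 1 + (c − 1) × ICC.
- Average over two equal groups, only one of them clustered: V = (1 + DE) / 2.
- True two-sided error of a nominal 5% test: 2 × [1 − Φ(1.96 / √V)].
- Power once clustering is allowed for: as in step 1, with λ = 8.112 / V.

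| Session size | ICC | DE | V | True error | λ | Power at 120 |
|---|---|---|---|---|---|---|
| 5 | 0.01 | 1.04 | 1.02 | 5.2% | 7.95 | 0.80 |
| 10 | 0.05 | 1.45 | 1.225 | 7.7% | 6.62 | 0.72 |
| 15 | 0.10 | 2.40 | 1.70 | 13.3% | 4.77 | 0.58 |

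These powers keep 118 error degrees of freedom. With 60 women in sessions of 5 to 15 there would be only 60/5 = 12 down to 60/15 = 4 sessions, so a proper analysis would have fewer degrees of freedom and somewhat less power than shown.

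**3. One sub-district per group (conditional; not stated in the text).** With 60 women per site, DE = 1 + 59 × ICC, where the ICC is that of change at site level, again assumed. True error = 2 × [1 − Φ(1.96 / √DE)].

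| Site ICC | DE | True error |
|---|---|---|
| 0.01 | 1.59 | 12.0% |
| 0.02 | 2.18 | 18.4% |
| 0.05 | 3.95 | 32.4% |

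Two sites minus two groups leaves 2 − 2 = 0 degrees of freedom between sites. The site variance cannot be estimated from the data, and more women per site would not change that.

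**The case against.** The strongest reply is that the article does not establish either feature. It never assigns sub-districts to groups, and Figure 1 might. The similarity of the sites would suit a pooled two-site study just as well, and the Abstract speaks of improvement across the selected sub-districts in the plural. With both groups recruited in balanced numbers in each site, site is not confounded with group, and leaving it out would tend to widen the error. Nor does the article say that several enrolled women share a session, how large sessions are, or which worker leads them. Some teaching is one-on-one, which would dilute any session effect. This all stands, and it is why both parts of the point are conditional.

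It is also true that the pre-post contrast removes stable differences between sites. Differential change over the 10 months remains, and the article itself calls both areas disaster-prone.

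Two further replies carry less weight. A fuller analysis plan could add a cluster term, but the sample size is fixed in this article, and a later model cannot restore power or create sites. Confounder adjustment is promised, and the limitations admit incomplete control of confounding and limited generalisability. Yet if site and group are the same variable, no adjustment separates them, and the limitations do not mention clustering.

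**Conclusion.** The point holds in conditional form. The sample size and the named ANOVA contain no allowance for session or sub-district, in a design with group sessions in one group only and two purposively chosen sites.

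If enrolled women share sessions and their changes are positively correlated, the standard error is too small. The size runs from negligible (5.2% error, power 0.80) to material (13.3%, power 0.58) over the assumed range, with a middle case of 7.7% and 0.72. The power figures also rest on the assumed alpha and correlation that reproduce 120.

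A reader might infer that site differences do enter the group effect, or that 12% to 32% is this study's error rate. The documents do not support that: it requires one sub-district per group, which the text never states, and ICCs that it does not give. A reader might also infer that intervention women are known to be taught together by one worker; the article says only that courtyard sessions are part of delivery.

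**What to change.** 1. **Sessions.** Record a session ID when education is delivered. The location data will not supply it: "Global positioning system mapping will be embedded in the questionnaire", and interviews are door-to-door, so GPS shows where a woman was interviewed and not which session she attended. Replace the plain ANOVA with a mixed model for change that has a session random effect in the intervention group only and a small-sample degrees-of-freedom correction, because sessions will be few.
2. **Mapping.** State how sub-districts map to groups. If both groups are in each, add sub-district and sub-district-by-time as fixed effects. In a model for change, the sub-district term already plays the sub-district-by-time role.
3. **If each group is one sub-district.** State that the p-value and confidence interval exclude between-site variation. Show the interval over assumed site ICCs: multiplying its width by √DE gives factors of √1.59 = 1.26, √2.18 = 1.48 and √3.95 = 1.99 for ICCs of 0.01, 0.02 and 0.05. Limit the conclusion to a comparison of two sites.
4. **Sample size.** State that 120 assumes independent women, and give the power over the assumed session ICC range. No additional enrolment is asked for.

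The cost is one recorded variable and some wording. The downside is wider intervals, a less favourable stated power and a more modest conclusion.

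### The 30% loss allowance multiplies 120 by 1.3 rather than dividing by 0.7, so at the protocol's own loss rate 156 recruits leave about 109 women, not 120

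*Protocol article*

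**What the plan says.** The Methods paragraph of the abstract describes a "quasi-experimental study with a sample size of 120 (60 - control, 60 - intervention"). It does not say whether 120 is the number to be recruited or the number to be analysed. The figure is not repeated in the body of the article.

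The Sample Size section says that G*Power was used and names the procedure ("Analysis of variance for repeated measures within-between interactions") with a Cohen's effect size of 0.13. It prints no significance level, target power or correlation between the two measurements. It then describes a substantial risk of loss, chiefly among the men. It sets the rate ("those lost to follow-up are regarded as 30" per cent) and reports the recruitment: "Considering the lost-to-follow-up rate, a total of 156 (78 - intervention and 78 - control) women and adolescent girls with disabilities were recruited".

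Under Design and setting, the allocation is equal: "The participant allocation ratio (intervention: control) will be 1:1".

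**The concern.** The article prints three numbers: 120, 30% and 156. They do not fit together if 156 is meant to leave 120 women after a 30% loss. The ratio of 156 to 120 is exactly 1.30, which suggests that 30% of the target was added on top. But 30% of the larger, recruited number is then lost, and that removes more women than were added.

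The recruitment figure is tied in the text to the loss rate, so a reader will take it that the planned loss has been covered. On the article's own figures it has not. If losses run as the article expects, the analysis will hold fewer women than the abstract shows, and a null result could be read as coming from a somewhat larger study than the one that was completed.

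**Working it through.** **Inputs from the article**
- Sample size 120, 60 per group (abstract, Methods).
- Loss to follow-up 30% (Sample Size).
- Recruited 156, 78 per group (Sample Size).
- Allocation 1:1 (Design and setting).
- Two measurements per woman (Data Analysis Plan).
- Effect size 0.13, repeated-measures ANOVA, within-between interaction (Sample Size).

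**Step 1. Reproduce the stated figure.** Adding 30% of the target: 120 × 1.30 = 156 and 60 × 1.30 = 78. Both match exactly. Dividing by the retained fraction gives 120/0.70 = 171.4, which does not match. That the article multiplied is an inference from this match, since it prints no formula.

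**Step 2. Apply the stated loss to those recruited.** 156 × 0.70 = 109.2 in total; 78 × 0.70 = 54.6 per group. The shortfall is 120 − 109.2 = 10.8 women, and 10.8/120 = 9%.

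**Step 3. Loss that 156 can absorb.** 1 − 120/156 = 0.231, so 120 is retained for losses up to 23.1%.

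**Step 4. Recruitment that would retain 120 at 30% loss.** 60/0.70 = 85.7, so 86 per group and 172 in total. Check: 172 × 0.70 = 120.4. This is 172 − 156 = 16 more than were recruited.

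**Step 5. What the shortfall does to power.** This step needs inputs that the article does not give. I assumed alpha 0.05, read 0.13 as f, and used the noncentral F distribution for the group-by-time interaction with two groups and m = 2 measurements:

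λ = N × m × f² / (1 − ρ), with 1 and N − 2 degrees of freedom.

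With ρ = 0.5, λ = 120 × 2 × 0.0169/0.5 = 8.11 at N = 120, and 109 × 2 × 0.0169/0.5 = 7.37 at N = 109. The smallest balanced N with at least 80% power is then exactly 120, which makes these settings a plausible source of the figure in the abstract but does not prove it. For the same 80% power, ρ = 0.3 would need 166 and ρ = 0.7 would need 72.

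| Pre-post correlation | Power at N = 120 | Power at N = 109 |
|---|---|---|
| 0.3 | 0.67 | 0.62 |
| 0.5 | 0.81 | 0.77 |
| 0.7 | 0.95 | 0.93 |

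The drop is about 4 percentage points at ρ = 0.3 and at ρ = 0.5, and about 2 points at ρ = 0.7.

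**The case against.** The best defence is that the 30% is a round judgement about the social setting and that the article expects the losses mainly among the men. The three outcome scales are answered by the women, whose losses may be lower, and 156 does keep 120 up to a 23.1% loss. Part of this stands: 109 is what the article's own rate implies, not a firm forecast. But the defence does not rescue 156. The article applies the rate to the count of women in both groups, and men are enrolled only in the intervention group, so male losses cannot explain 78 controls. Nothing in the article gives the women a lower rate or accepts fewer than 120.

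A second defence is that 120 appears only in the abstract and is never labelled as the evaluable target. That is true, and the label is an inference. If 120 were instead the number to be recruited, the abstract and the Sample Size section would disagree outright, and the text would still need correcting.

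This is also not a detail left to a fuller document. All three figures are printed in the article, and the issue is that they do not agree.

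**Conclusion.** The allowance is wrong as written. The finding that 156 recruits leave about 109 women at 30% loss, that 120 survives only up to 23.1% loss, and that 172 would be needed at 30%, rests on the article's own figures and on reading 120 as the evaluable target. The consequence is modest: about 11 women, and roughly 2 to 4 points of power over the correlations examined. It should be fixed, but it invalidates no test or estimate.

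Two stronger readings are tempting and are not supported.

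- A reader might infer that the trial misses its stated power. The article states no power, alpha or correlation. The fall from 0.81 to 0.77 depends on assumed inputs, and at N = 109 power runs from 0.62 to 0.93 as the correlation goes from 0.3 to 0.7. The value 0.77 cannot be attributed to the sponsor.
- A reader might also infer that the effect size is mislabelled, from "Analysis of variance for repeated measures within-between interactions assumed a medium Cohen's effect size of 0.13". The article does not name the metric or give benchmarks for it, and the source it cites is not available here. That complaint cannot be settled from the document, and the arithmetic above does not depend on it.

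**What to change.** In the Sample Size section and in the abstract, replace the present figures with a statement to this effect: 156 women and girls recruited (78 per group); 120 (60 per group) is the evaluable target, retained for losses up to 23%; at the assumed 30% loss about 109 (54 to 55 per group) remain.

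Report the power at about 109 from the alpha, target power and correlation that the sponsor actually entered in G*Power, and print those inputs. The values assumed above should not be written in as the sponsor's own.

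This is a change of wording with no further recruitment, and the article already says that important amendments will be published with the results. If enrolment is still open and the sponsor wants 120 evaluable women at 30% loss, the alternative is 172 recruits (86 per group), which costs 16 more participants.
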